## Abstract

**Background:**

Rising rates of sexually transmitted infections (STIs) among adolescents and young adults are concerning. Emergency department (ED) visits offer a unique opportunity to increase STI testing. However, providers in the ED may not have the time or self-efficacy to screen patients, and patients may be unable to initiate discussion on their STI care needs. A patient decision aid may improve the effectiveness and efficiency of the ED encounter for STI testing.

**Objective:**

This study aims to pilot STI Check in the Emergency Room (STIckER) app, a shared decision-making aid for urinary, oral, and rectal gonorrhea and chlamydia testing among adolescents and young adults, and assess STIckER’s efficacy and implementation outcomes in an adult and pediatric ED.

**Methods:**

We are conducting a parallel-group, two-arm provider-randomized controlled pilot trial in the adult and pediatric EDs at an urban academic medical center. Fifty providers were randomized 1:1 to intervention (trained on STIckER) or control (standard of care). Adolescents and young adults aged 14‐24 years, English-speaking, and sexually active within the past 6 months are recruited during eligible shifts and assigned to the study arm of their provider. The standard of care comparator consists of usual provider-initiated STI discussions and testing without access to the decision aid; control participants receive a QR code directing them to a simple landing page encouraging them to ask their provider about STI testing. The planned enrollment target was 44 providers and 140 adolescent and young adult participants. Primary outcome is preliminary efficacy, defined as the proportion of adolescents and young adults receiving gonorrhea and chlamydia testing based on electronic medical record (EMR) review. Secondary outcomes include extragenital testing uptake, STI positivity rates, decisional conflict, and perceived level of shared decision-making. Implementation outcomes include feasibility, acceptability, appropriateness (using acceptability of intervention measure, intervention appropriateness measure, and feasibility of intervention measure), and provider self-efficacy. Data will be analyzed using descriptive statistics and regression models, with mixed-effects models applied if clustering by provider is detected. Exploratory analyses will examine differences by patient age, gender, and sexual identity, and provider characteristics.

**Results:**

Between September 2023 and July 2025, we completed recruitment of 44 providers and 139 adolescent and young adult participants across both adult and pediatric EDs. Enrollment targets were met, with high fidelity to intervention delivery and strong rates of survey completion by both patients and providers. Final data cleaning and analyses are underway, and primary results are expected to be available in late 2025.

**Conclusions:**

This pilot trial will provide critical data on the feasibility, acceptability, and preliminary efficacy of a digital SDM tool to increase STI testing in the ED. Findings will inform the design of a future multisite trial and the potential for scaling STIckER to support equitable, patient-centered STI screening across diverse clinical settings.

## Introduction

Sexually transmitted infections (STIs) pose a significant and growing public health challenge in the United States. In 2022, more than 2.5 million cases of syphilis, gonorrhea, and chlamydia were reported nationally [1]. Gonorrhea and chlamydia require comprehensive screening to detect infections across multiple anatomic sites. Studies have shown that failure to conduct complete screening, including extragenital screening of oropharyngeal and anorectal sites, can lead to underdiagnosis. In fact, research suggests that if only urogenital screening is performed, more than one-third of infections may be missed [2].

Despite this, comprehensive gonorrhea and chlamydia screening, including 3-site screening, remains underused. Less than 5% of emergency department (ED) patients presenting with symptoms suggestive of extragenital infection undergo appropriate screening [3,4]. In outpatient settings, extragenital STIs are also prevalent but often undetected, with studies reporting prevalence rates as high as 77% among females and 22% among heterosexual males [3]. These data underscore the critical need for improved screening strategies that support multisite screening, particularly in settings where vulnerable individuals are likely to present.

The ED represents a vital yet underused venue for STI screening. Each year, over 19 million adolescents and young adults seek care in EDs, many of whom rely on these settings as their primary source of health care [4,5]. However, data suggest that the prevalence of STIs among adolescents and young adults in EDs ranges from 1.8% to 25%, representing substantial unmet need. Despite the potential for EDs to serve as access points for STI care, providers face substantial challenges to routine screening implementation. Time constraints, competing clinical priorities, lack of confidence in sexual history-taking, and discomfort discussing sexual health with patients all limit the integration of STI screening into ED workflows [6-9]. These limitations are especially problematic when caring for adolescent and young adult patients, who may face additional barriers including stigma, concerns around confidentiality, lack of knowledge about STI risks, and discomfort disclosing sensitive information in a high-acuity setting [10].

Novel strategies are needed to increase HIV and syphilis screening in the ED setting. While universal STI genitourinary testing minimizes patient stigma and provider bias, targeted testing recognizes the limited ED resources [11-13]. Furthermore, despite recommendations for universal opt-out HIV testing, fewer than 1% of ED patients are routinely screened. Researchers are currently focusing on clinical decision support (CDS) tools incorporated into the EMR [14]. While CDS tools are promising, they rely on each EMR system, thus leaving a gap in the care provided and missed opportunities for testing.

Shared decision-making (SDM) has been recognized as a valuable strategy for promoting patient-centered care, including for sexual health. However, implementing SDM in the fast-paced ED setting is difficult due to limited visit time, competing priorities, and a lack of standardized tools. Digital decision aids can help address these challenges by delivering tailored health education, collecting patient preferences, and streamlining communication with providers.

While decision aids have shown benefit in improving patient engagement and satisfaction in other ED contexts, including for decisions around chest pain, pain management, and syncope, there is limited work applying this approach to STI care [15-19]. No existing digital tool has been developed to support comprehensive gonorrhea and chlamydia screening, including extragenital screening, in the ED setting using an SDM framework.

To address these gaps, we developed STIckER (STI Check in the Emergency Room), a mobile, web-based decision aid designed to promote SDM between providers and adolescent and young adult patients in the ED. STIckER aims to support 3-site gonorrhea and chlamydia screening through a patient-centered approach grounded in evidence and stakeholder input. The tool guides users through an educational module, a sexual health risk assessment, and tailored screening recommendations, culminating in a provider-facing display that facilitates brief but informed shared decision-making. By front-loading STI education and risk assessment, STIckER reduces the time providers must spend initiating sensitive discussions and provides a standardized way to present testing options. Simultaneously, the app empowers adolescents and young adults by normalizing STI screening, increasing awareness of extragenital testing, and encouraging them to articulate their preferences. These features are designed to foster confidence in requesting testing and to facilitate efficient, values-based shared decision-making during time-limited ED encounters. STIckER was developed through an iterative process involving input from 19 adolescent and young adult patients and 7 ED providers [20]. By targeting known barriers to STI screening and supporting both patients and providers, STIckER aims to improve the delivery of equitable and complete STI care in the ED environment.

## Methods

### Trial Design

This parallel group, 2-arm, provider-level randomized controlled trial (RCT) was designed as a pilot evaluation to assess the preliminary effectiveness and implementation process of the STIckER app in an adult and pediatric emergency department (ED). The study followed CONSORT-eHEALTH guidelines V1.6 for reporting electronic and mobile health (mHealth) interventions.

### Participants

#### Provider Eligibility Criteria

A subset of health care providers (HCPs) was invited to participate. Eligible HCPs were attending physicians, residents, or nurse practitioners serving in the adult and pediatric EDs at NewYork-Presbyterian/Columbia University Irving Medical Center (NYP/CUIMC), a larger urban academic medical center in the Northern Manhattan section of New York City.

#### Patient Eligibility Criteria

Eligible patients were those being seen by an enrolled HCP, between ages 14 and 24 years, sexually active within the past 6 months (per self-report), able to speak English, and assigned a triage level of 3, 4, or 5. These triage levels indicate that the patient was not critically ill. Medical records were reviewed to identify potential subjects. Exclusion criteria include severe illness, cognitive impairment, or inability to speak English.

#### Providers Recruitment

HCPs were recruited via department meetings, email, and in-person outreach. All HCPs were educated about the study and viewed a recorded presentation on shared decision making and STI testing. HCPs who volunteered for enrollment provided written informed consent.

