### Intervention

Adolescents and young adults between the ages of 15 and 24 years attending the ED during the time that an HCP trained on STIckER was on service would scan the STIckER app before seeing the provider. patients as study participants (HCP-Ps and adolescent and young adult participants).

Adolescent and young adult participants are assigned to the arm of the provider to whom they are assigned. Adolescent and young adult participants with intervention-arm providers will scan a QR code with their personal mobile device, linking them to the web-based STIckER app. They will interact with the app, completing a sexual health assessment and indicating their personal values and preferences before being led to a final infographic to be shown to the HCP-P. This infographic will alert the provider to both the adolescent and young adult participants’ need for oral, rectal, or urinary STI testing and their preference for testing.

Adolescent and young adult participants with control-arm providers will also scan a QR code with their personal mobile device, but it will lead them to a landing page with a prompt informing them they can ask their provider about STI testing. They will not have access to the digital tools and shared decision-making modules within the STIckER app.

All adolescent and young adult participants are followed throughout the ED visit. Adolescent and young adult participants will complete questionnaires at enrollment and upon ED discharge. These questionnaires comprise a comprehensive set of predominantly validated instruments and will capture sociodemographic characteristics, sexual behavior, substance use, perceived HIV risk, patient satisfaction, and decision-making quality. HCP-P will also complete a questionnaire after each adolescent and young adult visit and an end-of-study questionnaire focused on STIckeR implementation.

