### STIckER Web-Based App

#### Control Participants

Participants in the control arm will scan a QR code and receive a statement reminding them they can always ask for STI testing.

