### Study Assessments

#### HCP-P Study Assessments

At enrollment, enrolled HCP-Ps will complete a basic demographic questionnaire. (age, race, ethnicity, sex at birth, gender identity, years since completing training, and type of clinical training completed).

The exit survey will be conducted immediately after a visit with an adolescent and young adult participant; the HCP-P will complete an exit survey.

HCP-Ps randomized to the control arm get questions on whether STI testing was discussed (“Did you and your patient discuss STI testing”), if the discussion was appropriate (Likert scale of 1‐5, from “completely appropriate” to “completely inappropriate”), if STI testing was ordered, and if STI testing was ordered what level of shared decision-making involvement occurred using the Control Preferences Scale (Likert scale of 1 to 5, from “I made the decision on my own” to “the patient made the decision on their own”) [22].

HCP-Ps randomized to the intervention will get the same questions on whether STI testing was discussed, if the discussion was appropriate, if STI testing was ordered, and if STI testing was ordered, what level of shared decision-making involvement occurred using the control preferences scale. They will also complete validated questions on implementation (acceptability of intervention measure [AIM], intervention appropriate measure [IAM], and feasibility of intervention measure [FIM]) [23].

The postsurvey will be conducted after completing their participation in the STIckER study (a maximum of 6 adolescent and young adult participants or the study completing overall enrollment), HCP-P will complete a postintervention questionnaire.

HCP-Ps, randomized to the control arm, will complete a self-efficacy questionnaire to measure their clinical communication skills [24].

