## Discussion

### Hypothesis

This protocol outlines an RCT to assess the preliminary efficacy and implementation of the STIckER app, a shared decision-making tool to support gonorrhea and chlamydia testing in adolescents and young adults in EDs. We anticipate that the intervention will lead to a higher proportion of adolescents and young adults receiving comprehensive genitourinary and extragenital STI testing compared to usual care, and that both patients and providers will find the tool acceptable, appropriate, and feasible to implement.

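### The comparator is labelled standard or usual care, but it is a prompted control with provider education and testing surveys in both arms, so the effect against unprompted usual care is not identified

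*Protocol article*

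**What the plan says.** The abstract (Methods) defines the comparator this way: "The standard of care comparator consists of usual provider-initiated STI discussions and testing without access to the decision aid". The same sentence goes on: "control participants receive a QR code directing them to a simple landing page encouraging them to ask their provider about STI testing". Power Analysis states the detectable difference relative to usual care. The Hypothesis section expects a higher proportion "receiving comprehensive genitourinary and extragenital STI testing compared to usual care".

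The procedures are set out elsewhere in the article:

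- Providers Recruitment: "All HCPs were educated about the study and viewed a recorded presentation on shared decision making and STI testing".
- Intervention, on the control patient's QR code: "it will lead them to a landing page with a prompt informing them they can ask their provider about STI testing". The Control Participants section says that they "receive a statement reminding them they can always ask for STI testing".
- Intervention, on providers in general: "HCP-P will also complete a questionnaire after each adolescent and young adult visit". HCP-P Study Assessments gives the control content: "HCP-Ps randomized to the control arm get questions on whether STI testing was discussed", and whether testing was ordered. Intervention providers get the same questions plus implementation scales. A provider finishes after at most 6 patients or when enrolment closes.

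Primary Outcome says that the estimate is meant to inform the design and sample size of a multisite trial.

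**The concern.** Usual care in an ED does not include a study page telling patients that they can ask for STI testing. Nor does it include a study presentation on the subject for providers, or a questionnaire after each visit about whether testing was discussed and ordered. All three bear on the primary outcome, gonorrhea or chlamydia testing.

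The prompt matters most because only control patients receive it as their whole allocation. It acts on a barrier that the article itself names: the abstract's Background says that patients may be unable to open the discussion. A comparator described as provider-initiated, whose patients are then encouraged to raise the topic, is at odds with its own description.

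Two uses of the result are at stake. A null or small difference could be reported as STIckER being no better than usual care, which the trial did not test. And the effect size could be carried into the multisite trial under a label that does not match the contrast that produced it.

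**Working it through.** **The plan's own figure.** Power Analysis gives a minimum detectable effect of 0.348 and interprets it against usual care. Inputs from that section: J = 44 providers, 140 patients, ICC 0.01, half of the variance explained at each level, two-sided α 0.05, power 80%. The standard two-level formula is

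MDES = M × √[4·ICC·(1−R²)/J + 4·(1−ICC)·(1−R²)/(J·n)].

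- With n = 3 patients per provider and the normal multiplier M = 1.960 + 0.842 = 2.802: √(0.02/44 + 1.98/132) = √0.01545 = 0.1243, and 2.802 × 0.1243 = 0.348.
- With n = 140/44 = 3.18 and a t multiplier on 42 df: 0.347.

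The figure reproduces. The formula has no term for what the control arm receives, so it cannot show which contrast the trial addresses. That has to come from the procedures.

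**What each arm receives.**

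| Component | STIckER arm | Control arm | In the abstract's account of the comparator? |
|---|---|---|---|
| Presentation on SDM and STI testing | yes | yes | no |
| Provider survey on STI testing after each enrolled patient | yes | yes | no |
| 1:1 training on the app | yes | no | not applicable |
| STIckER app | yes | no | stated as absent |
| Landing-page prompt about asking for testing | no | yes | yes, but under the standard-of-care label |

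**What the contrast estimates.** Write S for the shared components (presentation and surveys), and p(x, S) or p(x, no S) for the proportion tested when patients receive x with or without S. STIckER here includes the 1:1 training. Define

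- Δ_usual = p(STIckER, no S) − p(nothing, no S), the contrast that the usual-care label implies;
- a = p(STIckER, S) − p(STIckER, no S);
- b = p(nothing, S) − p(nothing, no S);
- c = p(prompt, S) − p(nothing, S).

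Then

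Δ_trial = p(STIckER, S) − p(prompt, S) = Δ_usual + (a − b) − c.

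- If the prompt raises testing at all, c > 0 and the estimate is smaller than it would be against an unprompted control.
- The term a − b can have either sign. It is zero if education and surveys lift both arms equally on the difference scale, positive if they work better alongside the app, and negative if the app leaves them less to add.
- The article gives no value for a, b or c and no usual-care testing rate. No arm receives neither the prompt nor S. So Δ_usual cannot be recovered from the trial's data.

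**Whether the article acknowledges this.** Strengths and Limitations covers language, scope, single site, blinding, engagement, multiplicity, provider training, staff support and device access. It notes that routine settings lack the training and research staff behind the app. It does not say that the control arm also departs from routine care.

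**The case against.** The best defence has four parts.

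First, the prompt is disclosed in the very sentence that defines the comparator, so no reader is misled about what control patients saw. That is true of the prompt, but not of the presentation and surveys, which are never presented as part of the comparator. Power Analysis and Hypothesis then say usual care without qualification.

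Second, the presentation and surveys are in both arms, so they do not bias the randomised comparison. This stands, and it limits the point. A reader might infer that all three components inflate control testing and that the trial therefore understates the benefit of STIckER. The documents do not support that: only the prompt is specific to control, and the shared components may raise testing in either arm. For the same reason, a sample-size calculation that lifts an assumed control rate while holding the STIckER rate fixed shows nothing about this trial. An equal lift in both arms leaves the difference unchanged.

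Third, the prompt is mild. Two of its three descriptions say only that patients can ask; the abstract alone says that they are encouraged. It would be too strong to say that the prompt turns every discussion into a patient-initiated one. Its effect may be small, but that is unknown.

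Fourth, if the multisite trial keeps the same prompted control, this is the right effect size for it. That is correct, and it is a reason to name the contrast accurately. The article does not state the future comparator.

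**Conclusion.** The comparator is mislabelled, and the claim should be narrowed. The trial validly estimates STIckER plus 1:1 training against a prompted control, with provider education and repeated surveys in both arms. A reader might conclude that the trial is invalid or that its estimate is certainly too small; neither follows.

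The gap between this contrast and the usual-care one is (a − b) − c. The prompt's part tends to reduce the estimate, the shared part is uncertain in sign, and the documents size neither.

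The conclusion rests on reading *all HCPs* as including control providers, since no exemption is stated. The downward tendency from the prompt also assumes that it reaches patients while they can still act on it. The article leaves this unclear: Participant Recruitment has patients approached after the provider has assessed them, while Intervention has the app scanned before the provider is seen.

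**What to change.** 1. In the abstract (Methods), Power Analysis and Hypothesis, replace standard of care or usual care with *enhanced (prompted) usual care*, and delete *usual provider-initiated* from the abstract's definition.
2. Limit the primary conclusion to that contrast, and say in Primary Outcome that the effect size carried to the multisite trial refers to it. A null result should then read as no detected advantage over a prompted control.
3. Add the patient prompt, the presentation and the post-visit provider surveys to Strengths and Limitations. State that the effect against unprompted usual care is not identified.
4. Optionally, if approvals allow, report the EMR testing proportion for the same providers before the study as descriptive context only. It would be non-randomised and not restricted to consenting patients who report sexual activity, so it should not be used to correct the estimate.

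An analysis by patient order within provider is not worth adding. The survey is in both arms, and order is confounded with calendar time and with growing familiarity with the app.

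Cost: items 1 to 3 are wording, and item 4 is one aggregate query. Enrolment and follow-up are complete and analysis is under way, so trial conduct does not change. The downside is a narrower claim.
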